## Abstract

**Background:**

Depressive disorders are one of the leading causes of disease and disability worldwide. In Vietnam, although epidemiological evidence suggests that depression rates are on par with global averages, services for depression are very limited. In a feasibility study that was implemented from 2013 to 2015, we found that a Supported Self-management (SSM) intervention showed promising results for adults with depression in the community in Vietnam.

This paper describes the Mental Health in Adults and Children: Frugal Innovations (MAC-FI) trial protocol that will assess the effectiveness of the SSM intervention, delivered by primary care and social workers, to community-based populations of adults with depression in eight Vietnamese provinces.

**Methods/design:**

The MAC-FI program will be assessed using a stepped-wedge, randomized controlled trial. Study participants are adults aged 18 years and over in eight provinces of Vietnam. Study participants will be screened at primary care centres and in the community by health and social workers using the Self-reporting Questionnaire-20 (SRQ-20). Patients scoring >7, indicating depression caseness, will be invited to participate in the study in either the SSM intervention group or the enhanced treatment as usual control group. Recruited participants will be further assessed using the World Health Organization’s Disability Assessment Scale (WHODAS 2.0) and the Cut-down, Annoyed, Guilty, Eye-opener (CAGE) Questionnaire for alcohol misuse. Intervention-group participants will receive the SSM intervention, delivered with the support of a social worker or social collaborator, for a period of 2 months. Control- group participants will receive treatment as usual and a leaflet with information about depression. SRQ-20, WHODAS 2.0 and CAGE scores will be taken by blinded outcome assessors at baseline, after 1 month and after 2 months. The primary analysis method will be intention-to-treat.

**Discussion:**

This study has the potential to add to the knowledge base about the effectiveness of a SSM intervention for adult depression that has been validated for the Vietnamese context. This trial will also contribute to the growing body of evidence about the effectiveness of low-cost, task-shifting interventions for use in low-resource settings, where specialist mental health services are often limited.

**Trial registration:**

Retrospectively registered at ClinicalTrials.gov, identifier: NCT03001063. Registered on 20 December 2016.

**Electronic supplementary material:**

The online version of this article (doi:10.1186/s13063-017-1924-5) contains supplementary material, which is available to authorized users.

## Background

Depressive disorders contribute considerably to the global burden of disease, and are expected to become the leading cause of Disability-adjusted Life Years (DALYs) worldwide by 2030 [1]. Despite the high prevalence of depression and its detrimental impact on quality of life, services for depression are limited in much of the world, particularly in low- and middle-income countries (LMICs) [2]. Mental health specialists are often in short supply, with services concentrated in often inaccessible and overburdened tertiary-care facilities [3, 4]. As a response to this treatment gap, task-shifting approaches, whereby nonspecialist providers deliver evidence-based and cost-effective services, have been recommended [5–7].

While epidemiological evidence about the prevalence of common mental disorders in Vietnam is limited, existing studies suggest that prevalence is similar to that found in much of the world, with rates of approximately 20% identified in some studies [8–10]. Mental health specialist services are limited, with the mental health system predominantly addressing psychotic disorders and epilepsy in tertiary-care facilities [3, 11]. Although patients with severe depression might receive pharmacological treatment in tertiary-care facilities, counseling and psychosocial interventions are almost nonexistent [11]. In its National Mental Health Strategy for 2015–2020, the Government of Vietnam has prioritized the enhancement of community-based mental health services including services for people with depression.

Supported Self-management (SSM) for depression is an approach through which providers support people with depression to learn and implement mood management skills [12]. SSM is a low-cost intervention that is consistent with guidelines for chronic illness care [13, 14]. It is appropriate for use in primary care settings by nonspecialist providers [15] and fits with a stepped-care approach that has been recommended for mental health service delivery in both high-income countries [16, 17] and LMICs [6, 18, 19]. In a systematic review, Lucock et al. (2011) [15] found that SSM produces an effect size that is on par with conventional depression treatment.

The SSM approach is fitting for community-based settings in LMICs, as it requires minimal resources, can be implement by primary care or lay providers using a task-shifting approach, and can be adapted to meet local settings. A SSM approach is consistent with the call by the global health community for “frugal innovations” that use few resources to meet pressing challenges [20, 21]. Evidence about the effectiveness of SSM in LMIC settings, however, is needed.

From 2013 to 2015, we conducted a pilot study in Hanoi, Vietnam to test the feasibility of training primary care providers to screen for, and treat, mild-to-moderate depression using SSM. The pilot study also tested the feasibility of conducting a full-scale randomized controlled trial (RCT), including the feasibility of primary care provider and patient recruitment. The pilot study demonstrated proof of concept and the SSM intervention was found to be acceptable and effective for use in Vietnam. At baseline, patient (*n* = 71) scores on the Self-reporting Questionnaire-20 (SRQ-20), a measure of depression symptoms that has been validated in the Vietnamese context [22, 23], varied from 8 to 17 (out of a possible 20) with a mean score of 10.9. Administrative errors led to a failure to obtain routine follow-up of SRQ-20 scores at the planned 2-month time period, but follow-up scores were eventually obtained for all participants (time between scores varied from 62 to 241 days). Upon follow-up, SRQ-20 scores varied from 1 to 13 with a mean score of 4.7, with 62/71 (87%) patients having SRQ-20 scores in the normal range.

The World Health Organization’s Disability Assessment Scale (WHODAS 2.0) [24] is a generic assessment instrument for health and disability across all diseases, including mental, neurological and addictive disorders. Scores are calculated in six separate domains (cognition, mobility, self-care, getting along, life activities and participation) and an overall score is based on the separate domain scores. Over the 2-month course of treatment, repeated measures analysis of variance (ANOVA) of the overall WHODAS 2.0 scores showed that the scores declined statistically significantly with mean values indicating less illness over time. Mean overall scores, which may vary from 36 to 180, dropped from 83.4 at baseline, to 71.9 after 1 month of treatment and 64.7 after 2 months. Separate repeated measures ANOVAs for the scores for the six subscales all showed at least one period with a statistically significant decline from baseline (see Fig. 1 for a plot of the means and 95% CIs for each of the domains).

**Fig. 1 Fig1:**
[figure not shown]
World Health Organization’s Disability Assessment Scale (WHODAS 2.0) domain scores at 0 months and 2 months

The results of the feasibility study suggest that SSM might be a viable and effective approach to treating mild-to-moderate depression in Vietnam. Given the shortage of mental health specialist providers and the government priority to improve community-based care for depression, the delivery of SSM through a task-shifting model could contribute substantially to addressing the depression treatment gap in Vietnam. This paper describes the study protocol of an RCT testing the effectiveness of the SSM intervention for treating mild-to-moderate depression in eight Vietnamese provinces. Based on the results of the feasibility study, we hypothesize that SSM would be more effective than treatment as usual in the treatment of mild-to-moderate depression in community-based settings in Vietnam.

## Methods/design

### Study setting

The purpose of this study is to test the effectiveness of the SSM intervention to treat mild-to-moderate depression in Vietnamese community-based populations. The SSM intervention will be tested in eight provinces across Vietnam (see Table 1). The study will take place in two districts of each province, targeting two communes (municipal subdivisions) in each district for a total of 32 communes.

**Table 1 Tab1:** Study provinces by region

Northern provinces	
Thanh Hoa	
Thai Nguyen	
Quang Ninh	
Central provinces	
Da Nang	
Quang Nam	
Khanh Hoa	
Southern provinces	
Long An	
Ben Tre	

### Design

The study uses a cluster-randomized, stepped-wedge controlled trial design. Randomization will occur at the commune level and communes will be assigned to receive either the SSM intervention first or the control condition first. The control condition will be enhanced treatment as usual. Those communes assigned to receive the control condition first will receive the SSM intervention 4 months later. This will ensure that the study is conducted ethically and will not deny evidence-based services to members of the control group. Participants in the intervention and control groups will be from different communes, or municipal districts, meaning that they do not access the same service units. This will minimize the risk of contamination. Figure 2 shows how the design will operate. The *black rows* depict the experimental data collection periods, *diagonally striped rows* are the control data collection periods, and the *gray rows* represent the long-term data collection period. The primary measure of interest is the proportion of individuals in the experimental versus the control group (*black* versus *diagonal striped*) that went from being a case of depression (SRQ-20 > 7) to being non-case (SRQ-20 < 8) over the experimental data collection period. Based on the feasibility case rate of a mean of one case every 14 days, each commune is expected to have eight completed cases (baseline, month-1 and month-2 measures) per year for a total *n* of 256 cases. Figure 3 shows a SPIRIT figure depicting the study design. Additional file 1 provides an overview of the elements of the study protocol, as described in a SPIRIT checklist.  Recruitment will continue until the desired sample size is reached and data can be analyzed to assess the effectiveness of the intervention.

**Fig. 2 Fig2:**
[figure not shown]
Study design

**Fig. 3 Fig3:**
[figure not shown]
SPIRIT Figure: MAC-FI Study Protocol

### Characteristics of participants

This study will test the effectiveness of a SSM intervention for reducing depression among adults in Vietnam. The study group consists of adult patients over the age of 18 years in 32 communes in eight Vietnamese provinces. Patients will be recruited by primary care providers at Commune Health Stations (CHSs), and by social workers in the community. Primary care providers at CHSs will screen patients during regular consultations, while social workers will screen community members who have been identified as vulnerable (e.g., new mothers, people experiencing bereavement, economic loss). Based on the results of the feasibility study, we do not anticipate major difficulty in recruitment. However, should recruitment prove challenging in some communes, we will expand the study to additional communes and consider expanding the duration of the study to ensure that we reach our target sample size.

### Outcome assessment

Demographic measures for both treatment and control clusters will be collected at baseline and will include: age, sex, education and economic status. The outcome measures will be collected at baseline, at 1 month and at 2 months following the initiation of SSM. The primary outcome measure will be the SRQ-20 Vietnamese version [22]. We selected the SRQ-20 as the most suitable measure following an extensive review of existing measures for depression [25]. The SRQ-20 has been carefully developed for use in Vietnam, it has been adapted to address culturally appropriate manifestations of depression symptomatology and its validity has been tested in studies within Vietnam [23]. As described above, through our feasibility study, we have good information about its performance and utility in Vietnam. We will also use the WHODAS 2.0 as a secondary measure to evaluate changes in functional ability [24]. This aspect of outcome is important as it allows an evaluation of important changes in an individual’s ability to perform activities of daily living and return to social and occupational activities. We have experience using the WHODAS 2.0 in our feasibility study and found that it provided meaningful information about changes in function with treatment. We have also added the Cut-down, Annoyed, Guilty, Eye-opener (CAGE) Questionnaire, a four-item alcohol misuse questionnaire [26] to the WHODAS 2.0, as research suggests that alcohol misuse and depression are related in Vietnam, especially among men [27]. The addition of the CAGE will help us to better understand the extent to which depression and alcohol misuse co-occur. Adverse events will be collected using a form for adverse events at each assessment point and any adverse event related to the intervention will be reported. We experienced no adverse events in our feasibility study.

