### Control condition

The control condition will be enhanced treatment as usual. For the most part, depression is not recognized or treated in primary care centres in Vietnam and it is, therefore, likely that patients who are receiving primary care at CHSs or who have been screened by social workers in the community in communes that are randomized to the control condition will receive little or no treatment for depression. Enhanced treatment as usual will consist of the following:Health and social workers will receive training that recommends “watchful waiting,” except in severe cases, including suicidal ideation, psychosis and the possibility of causing harm to others. Training will also include information about how to respond to emergency situationsPatients will receive a leaflet adapted from the *Beyond Blue “Understanding Depression”* Leaflet (www.beyondblue.org.au) that provides information about depression, providing patients with information about their diagnosis, including depression symptoms, risks and approaches to treatment

Patients in communes randomized to the control condition will be offered SSM following the period of control data collection, after 4 months. At the time of the 1- and 2-month assessments, we will capture what, if any, additional treatment has been accessed by the patient (e.g., services at the tertiary-care level, informal or formal counseling, supplements, traditional Vietnamese interventions, sleeping pills). Concomitant care is not prohibited during the trial, but the study team will record any formal or informal treatments and services that might be accessed by patients during their enrollment in the study.

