### Blinding

It will not be possible to institute full blinding because of the nature of the intervention. Project outcome assessors will be blinded. Based in the project head office in Hanoi, outcome assessors will conduct the 1- and 2-month assessment interviews with patients by telephone. The outcome assessors will have no information about patients, where they are located or whether they are allocated the intervention or control condition. The project research coordinator will collect telephone numbers from the participants, and will assign them an appointment with the outcome assessor. The outcome assessor will then call the telephone number with no additional information about the participant. Participants will be instructed not to share information about whether they are part of the intervention or control group with outcome assessors to avoid contamination.

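### Adverse events are collected in both arms, but the only reporting commitment covers events related to the intervention, so following it alone would give a one-sided harms report

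*Protocol article*

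**What the plan says.** Under Outcome assessment, one sentence of the protocol article sets two rules. The first concerns collection: "Adverse events will be collected using a form for adverse events at each assessment point". It has no limit by arm or by cause. The second concerns reporting: "any adverse event related to the intervention will be reported". No other section makes a commitment on reporting adverse events. The Analysis section names SRQ-20, WHODAS 2.0 and CAGE as the outcome variables. It defers many details to the statistical analysis plan, but does not mention adverse events among them.

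The Control condition section describes enhanced usual care as staff training that recommends watchful waiting, plus a leaflet for patients. It expects that control patients "will receive little or no treatment for depression". SSM is offered to them after 4 months. The same section confirms that they are followed up: "At the time of the 1- and 2-month assessments, we will capture what, if any, additional treatment has been accessed by the patient".

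Under Inclusion and exclusion criteria, the article foresees that enrolled patients may become suicidal or psychotic, in which case they are referred to tertiary care. Those treated there leave the study, and the article accepts that following them up may be difficult.

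**The concern.** Collection is broad, but the reporting commitment is narrowed by relatedness to the intervention. Throughout the article, the intervention is SSM and the comparator is the control condition. During the control period a patient has had no SSM to which an event could be related. A rule keyed to relatedness therefore treats the two arms differently: an event in an SSM patient may qualify, while the same event in a control patient hardly can.

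At stake is whether readers can see if SSM raises or lowers harm relative to enhanced usual care. The events that matter most, such as new suicidality or psychosis, can easily be attributed to the underlying illness. In an SSM patient they could then be classed as unrelated, and in a control patient they would fall outside the rule. If SSM reduced such events, a report built on this rule could not show it.

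**Working it through.** No arithmetic applies, because the article gives no adverse-event rate for either arm. The check is to set the relevant statements side by side.

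1. **Are events collected in both arms?** The form is used at each assessment point. The abstract, having described both groups, says: "SRQ-20, WHODAS 2.0 and CAGE scores will be taken by blinded outcome assessors at baseline, after 1 month and after 2 months". The Control condition section refers to the 1- and 2-month assessments of control patients. Read naturally, the answer is yes. One phrase is awkward: Outcome assessment times the measures "at 1 month and at 2 months following the initiation of SSM", which does not fit a patient in the control period. The abstract and the Control condition section show that control patients are nevertheless assessed.

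2. **What is promised about reporting?** Only events related to the intervention are covered. The text is silent on collected events judged unrelated, on who judges relatedness, and on whether reporting means publication or notification to oversight bodies.

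3. **Can a control event qualify?** The control period contains no SSM, which is offered after 4 months, whereas the outcome assessments end at 2 months. An event found at a control patient's 1- or 2-month assessment therefore precedes any SSM and can hardly be related to it.

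4. **What does the rule give if followed alone?**

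| | SSM arm | Control arm, control period |
|---|---|---|
| Events collected | Yes, at each assessment | Yes, at each assessment |
| Covered by the reporting commitment | Those judged related | Essentially none |
| Collected events judged unrelated | No commitment | No commitment |

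5. **Does relatedness need knowledge of the arm?** Attributing an event to SSM requires knowing that the patient received it. The Blinding section says of the follow-up interviewers: "The outcome assessors will have no information about patients, where they are located or whether they are allocated the intervention or control condition". Someone other than a blinded interviewer would have to make the judgement, and the article does not name that person. This is compatible with the blinding plan. It does mean that what is reported would turn on a judgement made with knowledge of the arm, which reporting all events by arm avoids.

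6. **Does the feasibility study settle the matter?** The article says it saw no adverse events. As described, that study followed SSM-treated patients, with no comparison arm mentioned. It therefore gives no information on events under enhanced usual care.

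**The case against.** The strongest reply has four parts.

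- **The sentence is not exclusive.** It promises to report related events and does not say that others will be withheld. This is correct. A reader might infer that control-arm harms are excluded and that no comparison between arms is possible, but the documents do not support that. The form is used in both arms, so the data would be there to tabulate. For the same reason, a figure of zero reportable control events follows only if the sentence is applied as the sole rule.
- **Reporting may mean notification.** Relatedness is a usual trigger for notifying oversight bodies, and the text does not settle which sense is meant. This also stands. On that reading, however, the article makes no commitment at all on harms in the results, and notification is still filtered by relatedness.
- **Safety tables usually belong in the analysis plan, which is not shown.** The absence of a table would indeed be no finding. The point here is a rule that the article does state. An analysis plan that followed it would carry the asymmetry forward.
- **Deterioration is captured elsewhere.** SRQ-20 and WHODAS 2.0 are measured in both arms and analysed by intention to treat, and tertiary services used are recorded. No judgement of relatedness can remove a worsened score. This limits the harm, but a scale score does not replace a count of events such as referral for suicidality, particularly when follow-up of those patients may be difficult.

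A reader might also infer that the blinded interviewers must judge relatedness and would be unblinded by doing so. The article assigns that task to nobody, so this does not follow.

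**Conclusion.** The point holds as a weakness in a stated reporting rule. Adverse events are captured in both arms, but the only reporting commitment depends on relatedness to SSM. Applied alone, it would yield a harms account essentially from one arm, selected by judgement, with no fair comparison.

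This rests on two readings: that the intervention means SSM, and that control patients complete the adverse-event form at their 1- and 2-month assessments. The document supports both. The size cannot be stated, since no event rates are given. Collection, blinding and the efficacy analysis are unaffected, and nothing in the article limits what the Data Monitoring Committee may see. The correction is worth making because it is cheap and no later section of the article repairs the rule.

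**What to change.** Change the sentence under Outcome assessment to say that all adverse events collected at the assessments, including referrals for suicidality or psychosis, will be reported by arm, with counts and proportions, whatever their judged relatedness. Show relatedness as an extra column, not as a condition for inclusion. State that the same by-arm table goes to the Data Monitoring Committee. If the present wording was meant as a rule for notifying oversight bodies, say so and keep it separate from the rule for results.

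The cost is one sentence and one table. The adverse-event form is already in use at each assessment point, so no change to the design, sample size or visit schedule is needed.
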